### Intervention

#### Laparoscopic exploration

Laparoscopic exploration is to detect occult peritoneal metastases and inspect the primary lesion, liver, diaphragm, pelvic organs, bowel and omentum according to the standard requirements reported before [21]. Patients with any patterns of distant metastases, suggestive of distant metastasis (M1), will be excluded from the trial and recommended to a multi-disciplinary team (MDT) for further treatment.

#### Surgery

A standard D2 radical open or laparoscopic gastrectomy will be planned 3–4 weeks after the last cycle of chemotherapy. Laparoscopic gastrectomy will be recommended. The extent of gastric resection and lymphadenectomy will be performed as per the treatment guidelines [22]. Reconstruction after gastrectomy will be decided by the surgeon. All operations will be performed by well trained and experienced surgical team to guarantee the quality of surgery, including harvesting more than 16 lymph nodes. The surgeon will determine if D2 lymphadenectomy is completed and photos of the surgical field after gastrectomy will be monitored and reviewed centrally.

#### Neoadjuvant chemotherapy

The preoperative SOX chemotherapy consists of three-week cycles of intravenously administered oxaliplatin 130 mg/m^2^ on day 1 and orally administered S-1 40–60 mg twice a day (BID) on day 1 to 14. The dose of S-1 depends on body surface area (BSA): 40 mg BID for BSA < 1.25 m^2^; 50 mg BID for 1.25 m^2^ < BSA < 1.5 m^2^; 60 mg BID for BSA > 1.5 m^2^. Day 15 to day 21 is the rest period.

### Tumor response and toxicity criteria

Lesions will be evaluated according to the RECIST 1.1 criteria after the third and the sixth cycle of SOX by enhanced CT, EUS, MRI as needed [19]. Toxicities are measured according to National Cancer Institute Common Toxicity Criteria for Adverse Event (NCI-CTC AE), version 4.0. AE will be recorded in the AE report form. Serious adverse events (SAE) are defined according to the rules of good clinical practice (GCP) and will be reported to the lead center within one working day, after which other centers will be notified promptly.

### Follow-up

After treatment, patients will be examined every 6 months for 5 years, then every 12 months for life. The follow-up will include enhanced CT/MRI, abdominal ultrasound, chest X-ray, physical and laboratory examination, according to the schedule (Table 1).

**Table 1 Tab1:** Follow-up schedule

Postoperative (years)	1			2		3		4		5	
Postoperative (months)	1	6	12	18	24	30	36	42	48	54	60
Body weight Complete blood count Biochemical test Tumor markers	√	√	√	√	√	√	√	√	√	√	√
Abdominal ultrasound		√	√	√	√	√	√	√	√	√	√
Abdominal CT/MRI	√	√	√	√	√	√	√	√	√	√	√
Chest X-ray			√		√		√		√		√

### Sample size calculation

The primary endpoint of this trial is pCR rate. Based on the data from previous study, after three cycles of SOX, the PCR rate is about 7% (*p*_*0*_), and we estimated that with six cycles of SOX, the PCR rate can be increased to 15% (*p*). Based on the Z test, the null and alternative hypotheses are *H*_*0*_: *p*=*p*_*0*_; *H*_*1*_: *p*≠*p*_*0*_. With the statistical power of 0.8 (β=0.2), the type I error rate of 0.05 (α=0.05), when *Z* > marginal value, the *H*_*0*_ will be rejected and *H*_*1*_ will be accepted. Using the following formulas with the sampling ratio is 1:1 and the drop-out rate of 10%, the sample size is set at 262 per arm [23].
$$ n=p\left(1-p\right){\left(\frac{z_{1-\frac{\alpha }{2}}+{z}_{1-\beta }}{p-{p}_0}\right)}^2 $$Each participant center takes 400 to 1000 cases of gastric cancer per year and about 2% of patients can be enrolled. Thus recruitment can be completed in 2 years.

### Statistical analysis

The pCR rate is defined as the rate of patients achieving pCR. The R0 resection rate is defined as the rate of R0 resection. The DFS is defined as the period from the time of surgery to recurrence or death. The OS is defined as the period from the time of surgery to death or last follow-up. Chi-square test will be used to compare patients’ characteristics, pCR rate and R0 resection rate between two arms. Survival curves will be estimated by the Kaplan-Meier method. Survival rate of DFS and OS will be compared respectively between two arms using a two-sided log-rank test. Both intention-to-treatment analysis (ITT, patients who receive any treatment after enrollment) and per-protocol analysis (PP, patients who receive all preoperative chemotherapy and surgery) will be performed. Missing data will be processed using multiple imputation. For loss of follow-up, ITT analysis and sensitivity analysis will be performed respectively.

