### Grouping

All eligible patients will be registered, pre-enrolled and receive three cycles of SOX. After tumor response evaluation using RECIST 1.1, patients achieving CR or PR will be enrolled [19]. Then randomization without stratification will be carried out by computer generated allocation using IBM SPSS Statistics 22, and enrolled patients will be randomly assigned (1:1) to Arm A or Arm B.

Arm A: Patients will be pre-enrolled and receive three cycles of SOX. After randomization, patients in Arm A will receive three more cycles of SOX (six cycles of neoadjuvant chemotherapy with SOX in total) followed by D2 gastrectomy. After which postoperative chemotherapy will not be recommended.

Arm B: Patients will be pre-enrolled and receive three cycles of SOX. After randomization, patients in Arm B will receive D2 gastrectomy (three cycles of neoadjuvant chemotherapy with SOX in total). After which postoperative chemotherapy using SOX will be recommended.

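### DFS and OS are timed from surgery, which follows randomisation and comes about 9 weeks later in Arm A, so the log-rank tests do not compare the arms as randomised

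*Protocol article*

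**What the plan says.** The Statistical analysis section fixes both clocks. For disease: "The DFS is defined as the period from the time of surgery to recurrence or death". For survival: "The OS is defined as the period from the time of surgery to death or last follow-up". Both are compared between arms with a two-sided log-rank test.

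The Grouping section puts randomisation after the third cycle and before surgery: "After tumor response evaluation using RECIST 1.1, patients achieving CR or PR will be enrolled", and these patients are then randomised 1:1. The arms part from there. "After randomization, patients in Arm A will receive three more cycles of SOX", whereas "After randomization, patients in Arm B will receive D2 gastrectomy". Under Neoadjuvant chemotherapy, "The preoperative SOX chemotherapy consists of three-week cycles". Under Surgery, the operation "will be planned 3–4 weeks after the last cycle of chemotherapy", with no distinction by arm.

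The Statistical analysis section also defines two analysis sets. The intention-to-treat set needs only some treatment after enrolment. The per-protocol set needs all preoperative chemotherapy and surgery.

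**The concern.** Time zero for both survival endpoints is an event that happens after randomisation, and the assigned arm itself delays it. Two things follow.

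- A patient who progresses or dies between randomisation and surgery contributes no event to DFS or OS. Arm A spends longer in that interval.
- A patient who is never operated on has no start date. The two analysis sets imply that the plan expects such patients, because one set requires surgery and the other does not. Multiple imputation and the sensitivity analysis for loss to follow-up do not supply a missing time origin.

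The trial asks whether longer preoperative treatment is better, and failing before surgery is one of the risks of that strategy. The Discussion hopes that Arm A's results may support giving chemotherapy only before surgery. That inference needs a survival comparison that keeps every randomised patient on the same clock.

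**Working it through.** **The plan's own figure.** The only sample-size figure is 262 per arm, and it rests on pCR. With 7% against 15%, two-sided α 0.05, power 0.80 and unpooled variance:

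n = (0.15×0.85 + 0.07×0.93) × (2.8016/0.08)² = 0.1926 × 1226.4 = 236.2; 236.2/0.9 = 262.4.

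This matches 262. No event number or power is stated for DFS or OS, so the time origin does not touch the sample size.

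**Offset between arms.** The 3–4 weeks from last cycle to surgery applies to both arms and cancels. What remains is 3 cycles × 3 weeks = 9 weeks = 63 days, or 63/30.44 = 2.1 months.

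**Illustration.** The protocol gives no failure, non-operation or DFS rates, so these inputs are assumptions:

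- S, the true event-free proportion 36 months after randomisation, is the same in both arms: 50, 60 or 70%.
- f, the proportion failing before surgery (A vs B): 5 vs 2%, 8 vs 2% or 10 vs 3%.
- t, the time from randomisation to surgery: B 0.8 months (3.5 weeks, with randomisation at the end of cycle 3); A 0.8 + 2.1 = 2.9 months.
- The hazard h is constant after surgery.

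Because S = (1−f)·exp(−h(36−t)), h = ln((1−f)/S)/(36−t). Three-year DFS from surgery is exp(−36h), and the apparent HR is h_A/h_B. Three years from surgery ends 38.9 months after randomisation in A and 36.8 in B.

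For S = 60% and 8 vs 2%:

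- A: h = ln(0.92/0.60)/33.1 = 0.4274/33.1 = 0.01291; DFS = 62.8%.
- B: h = ln(0.98/0.60)/35.2 = 0.4906/35.2 = 0.01394; DFS = 60.5%.
- Difference 2.3 points; HR 0.01291/0.01394 = 0.93.

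Full grid, as the spurious difference in points (A minus B) and HR:

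| True S | 5 vs 2% | 8 vs 2% | 10 vs 3% |
|---|---|---|---|
| 50% | −0.5 (1.01) | +1.3 (0.96) | +2.0 (0.94) |
| 60% | +0.1 (1.00) | +2.3 (0.93) | +3.2 (0.90) |
| 70% | +0.9 (0.97) | +3.4 (0.86) | +4.5 (0.82) |

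**When the artefact vanishes.** With one constant hazard from randomisation, equal in both arms, survival from surgery is identical in both arms. At S = 50–70%, about 2.8–5.4% of Arm A (7–14 of 262) and 0.8–1.5% of Arm B (2–4 of 262) would still fail before their clock started. Those events are lost, but the comparison is not shifted. A shift towards Arm A needs more pre-surgery failures there than its longer window alone would produce.

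**The case against.** The strongest reply has four parts.

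1. *DFS from surgery is a coherent measure.* A disease-free interval usually begins once disease has been removed. This stands for a description of resected patients. It does not justify a log-rank test between randomised arms, and it does not explain why OS starts there.

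2. *The endpoints are secondary, and only responders are randomised.* Both are true. The Discussion says that selecting responders should reduce early stopping of chemotherapy. A reduction is not abolition, and the analysis sets still allow for patients without surgery.

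3. *Pre-surgery failures are seen elsewhere.* A reader might infer that the definition hides this harm altogether. The document does not support that: safety and R0 resection rate are secondary endpoints, adverse events are recorded, and lesions are re-evaluated after the sixth cycle. What is lost is their place in DFS and OS.

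4. *The bias may be small or absent.* This stands. A reader might infer that it must favour Arm A, or might size it by dividing S by (1−f), which gives 0.60/0.92 − 0.60/0.98 = 65.2% − 61.2% = 4.0 points in the central case. That division holds the horizon at 36 months from randomisation, whereas the defined endpoint runs 36 months from surgery. With the right horizon the difference is 2.3 points, and one corner of the grid slightly favours Arm B.

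**Conclusion.** The defect is in the stated text and does not depend on any assumed rate. Both survival clocks start at a post-randomisation event that comes about 9 weeks later in one arm, early failures are left out over unequal windows, and unoperated patients in the intention-to-treat set have no survival time. The log-rank comparisons of DFS and OS are therefore not comparisons of the groups as randomised.

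The size and direction of the resulting bias are unknown. Under the assumed rates above, the artefact in 3-year DFS is about −0.5 to +4.5 points (HR 1.01 to 0.82), and 2.3 points (HR 0.93) in the central case. It favours Arm A only if Arm A's pre-surgery failures exceed what its longer window would produce anyway. The primary pCR analysis and the 262 per arm are unaffected.

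**What to change.** - **OS:** measure from randomisation to death in all randomised patients, censoring at last follow-up.
- **Disease comparison between arms:** use event-free survival from randomisation in all randomised patients, counting progression that precludes resection, recurrence and death. Whether a non-R0 resection counts as an event is for the sponsor to prespecify; the protocol does not settle it.
- **DFS from surgery:** keep it as a descriptive analysis of resected patients.

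Treatment and sample size do not change. There are two costs. Survival figures will look slightly less favourable, because early failures now count. Unoperated patients also need follow-up dated from randomisation, because Table 1 counts only postoperative months. The protocol does not say that the reason for not operating is recorded, so the case report form should be checked for it.

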## Methods

RESONANCE-II trial is a prospective, multicenter, randomized, controlled phase III study which will be conducted in 29 medical centers in China and one medical center in Korea. Chinese PLA General Hospital is the lead center. [name] is the trial principal investigator (PI). All screened patients should state that they are healthy and have no discomfort, then they will sign the informed consent. After signing the informed consent, they will receive consultation from investigator and examinations. Eligible patients will be registered, pre-enrolled. Main possible reasons for screening failure include: (1) The results of physical examination or laboratory tests do not meet the inclusion criteria or meet the exclusion criteria; (2) Patients withdraw informed consent or refuse to participate in the research.

Pre-enrolled patients will receive three cycles of SOX. Then, tumor response evaluation will be carried out according to the Response Evaluation Criteria for Solid Tumors (RECIST) 1.1 [19]. Those who demonstrate stable disease (SD) or progressive disease (PD) will be excluded. Patients achieving complete response (CR) or partial response (PR) will be enrolled and assigned into either group A (six cycles of neoadjuvant chemotherapy with SOX) for another three cycles of SOX followed by D2 surgery or group B (three cycles of neoadjuvant chemotherapy with SOX) for D2 surgery. Figure 1 showed the study flow chart. The trial has been approved by the ethics committee of the Chinese PLA General Hospital, Beijing, China and registered prospectively in the World Health Organization International Clinical Trials Registry Platform (WHO ICTRP) with registration number ChiCTR1900023293 on May 21st, 2019. All patients are required to sign the written informed consent.

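### The set called ITT has a different entry event in each arm (starting cycle 4 in Arm A, in effect the operation in Arm B), so pCR and R0 are not compared as randomised

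*Protocol article*

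**What the plan says.** The protocol article separates pre-enrollment from enrollment. Methods states: "Pre-enrolled patients will receive three cycles of SOX". Grouping then states: "After tumor response evaluation using RECIST 1.1, patients achieving CR or PR will be enrolled", and that "enrolled patients will be randomly assigned (1:1) to Arm A or Arm B". Cycles 1 to 3 are therefore given before enrollment.

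The assigned treatments after that point differ in kind. For Arm A: "After randomization, patients in Arm A will receive three more cycles of SOX", with D2 gastrectomy afterwards. For Arm B: "After randomization, patients in Arm B will receive D2 gastrectomy".

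Statistical analysis names two sets. One is an "intention-to-treatment analysis (ITT, patients who receive any treatment after enrollment"); the other is a "per-protocol analysis (PP, patients who receive all preoperative chemotherapy and surgery"). The article describes no set of all randomised patients. It assigns missing data to multiple imputation and gives no rule for how a patient without resection counts towards pCR or R0. DFS and OS are both timed from surgery.

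**The concern.** A set restricted to treated patients can be tolerable when the entry event is the same in both arms and occurs soon after randomisation. Here it is neither. In Arm A the entry event is the first dose of cycle 4. In Arm B it is the operation, which is also what makes the primary endpoint observable, because pCR is graded on the resected specimen.

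Consider two patients with the same course who become unfit for surgery or refuse it. In Arm B, with nothing further given, the patient leaves the denominator. In Arm A, once cycle 4 has begun, the patient stays in it without a pCR. Selection then depends on arm and on events after randomisation that are plausibly linked to prognosis.

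The per-protocol set, restricted to "patients who receive all preoperative chemotherapy and surgery", does not correct this. Arm A must complete three further cycles plus surgery to qualify, Arm B only surgery. At stake is whether the primary comparison (pCR) and the R0 comparison rest on the randomised groups.

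**Working it through.** **Inputs from the article (Sample size calculation).** pCR 7% after three cycles and 15% after six; two-sided α = 0.05; power 0.80; drop-out 10%; 262 per arm.

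**The plan's own figure.** The two-sample unpooled formula gives n = [0.15×0.85 + 0.07×0.93] × (1.960 + 0.842)² / 0.08² = 0.1926 × 7.849 / 0.0064 = 236.2, and 236/0.9 = 262. The stated size is reproduced as a two-arm comparison. (The printed formula, with p(1−p) alone, gives 156.4 and does not lead to 262; that is a separate matter.) Pooled-z power for 15% vs 7% is 83.5% at 262 per arm.

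**Assumptions, because the documents give no non-operation rate.**
- The same share u in each arm is never operated on.
- pCR among operated patients is 15% (A) and 7% (B).
- Unoperated patients count as non-pCR.
- Every Arm A patient starts cycle 4.
- Unoperated Arm B patients receive nothing else.

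**Formulas.**
- All randomised: A = 0.15(1−u), B = 0.07(1−u), 262 per arm; difference 0.08(1−u).
- As written: A = 0.15(1−u) on 262, B = 0.07 on 262(1−u); difference 0.08(1−u) − 0.07u.
- Power = Φ[(difference − 1.96·s₀)/s₁], where s₀ is the pooled and s₁ the unpooled standard error.

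**Worked case, u = 10%.**
- All randomised: 13.5% vs 6.3%, s₀ = 0.02609, s₁ = 0.02590; (0.072 − 0.05114)/0.02590 = 0.805, power 79.0%.
- As written: 13.5% of 262 vs 7.0% of about 236, s₀ = 0.02743, s₁ = 0.02687; (0.065 − 0.05375)/0.02687 = 0.419, power 66.2%.

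| u | Difference, all randomised | Power | Difference, as written | Power |
|---|---|---|---|---|
| 2% | 7.84 points | 83% | 7.70 points | 81% |
| 5% | 7.60 | 81% | 7.25 | 76% |
| 10% | 7.20 | 79% | 6.50 | 66% |
| 20% | 6.40 | 74% | 5.00 | 44% |

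**Unequal rates.** Only the untreated share of Arm B is dropped, so that share drives the loss. With 10% unoperated in Arm A throughout:
- 2% untreated in Arm B: power 71.1% as randomised, 68.5% as written.
- 5% untreated in Arm B: 74.2% and 67.7%.

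**No true difference.** If pCR is 10% of all randomised patients in both arms and u = 10%, the written rule shows 10.0% of 262 vs 10/0.9 = 11.1% of about 236. The two-sided rejection rate is about 6.9% instead of 5%, with the shift against six cycles.

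**R0.** By the same algebra the artificial gap is u times the R0 rate among operated patients. As an illustration only, take the 81.9% that Background quotes for the neoadjuvant arm of another trial, and treat it as the rate among operated patients in both arms. At u = 10% the gap is 0.10 × 81.9 = 8.2 points (73.7% in A, 81.9% in B) with no true difference.

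**The case against.** The strongest reply is that the rule says any treatment, not the assigned treatment. An unoperated Arm B patient who is given something else after enrollment stays in on a literal reading, and an Arm A patient who never starts cycle 4 is dropped as well. Both points stand. A reader might infer that the rule removes every unoperated Arm B patient and keeps every unoperated Arm A patient; the text does not support that. The asymmetry is between Arm B patients with no treatment after enrollment and Arm A patients lost after cycle 4 starts.

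A second reply is that the size is assumed. This also stands. The 10% in the article is a general drop-out allowance, not a non-operation rate, and exposure before surgery is longer in Arm A. If few Arm B patients go untreated, the loss is 2 to 3 points of power. Counting unoperated patients as non-pCR is also an assumption. If they were imputed the size would change, but the excluded patients would still be missing from the set.

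A third reply is that DFS and OS are not distorted by this wording in particular. That is right: with time running from surgery, an unoperated patient has no time origin in either arm, whichever set is used.

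Finally, the article does not say which of its two sets is primary. That is detail commonly left to the full protocol or analysis plan, and it is not a fault here.

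The definition of the set itself is different, because the article states it. Reading enrollment as pre-enrollment would remove the asymmetry, but Methods and Grouping contradict that reading.

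**Conclusion.** The point holds for pCR and R0. The stated set is not an intention-to-treat set; its entry event differs by arm, and in Arm B it largely coincides with being operated on. The per-protocol set is also unequal between arms and cannot serve as the correction.

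Under the listed assumptions the loss of power runs from about 2 points at 2% unoperated to 13 points at 10% and 30 points at 20%, and the bias is against six cycles, the arm expected to do better. These are scenarios. A reader might take 66% as the trial's actual power, but the documents do not supply the rate that would justify it. A reader might also infer that the two sets are biased in opposite directions and so bracket the truth; the per-protocol bias has not been quantified, so this is not shown.

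**What to change.** Define ITT as all randomised patients in their allocated arm, whether or not any treatment followed randomisation, and use it for the main pCR and R0 comparisons. State that a patient without resection counts as non-pCR and non-R0 and is not imputed; imputation can remain for resected patients whose result is missing. Keep the set of patients treated after enrollment for safety or as a sensitivity analysis, and label the per-protocol analysis as supportive.

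For DFS and OS, the all-randomised set works only if time is also measured from randomisation instead of surgery, so those two definitions must change with it.

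The cost is a short change of text before the data are analysed, with no additional patients. The downside is that reported rates become slightly less favourable: at 10% unoperated, 13.5% and 6.3% instead of the 15% and 7% assumed among operated patients.

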## Discussion

The RESONANCE-II study was conducted to evaluate the efficacy and safety of different cycles of SOX as neoadjuvant chemotherapy for patients with locally advanced gastric cancer. The primary endpoint of the study is the rate of pathological complete response. A study evaluated the histopathological tumor regression in 480 gastric cancer patients who received surgery after neoadjuvant chemotherapy. The results showed that complete or subtotal tumor regression was an independent prognostic factor for survival, which suggested that pathological complete regression could be regarded as a proper endpoint for neoadjuvant trials in gastric cancer [24]. Moreover, our study aims to evaluate the efficacy of preoperative chemotherapy. Using pCR rate as the primary endpoint instead of survival could reduce the influence of surgery and postoperative chemotherapy on the endpoint. Also, less time will be required to get the primary results. Therefore, we chose pCR rate as the primary endpoint. However, to illustrate the relation between tumor regression and survival thoroughly, further research is still needed.

In our study, eligible patients will be pre-enrolled and receive 3 cycles of SOX. Those who achieve CR or PR will be enrolled and considered as subjects with cancer that is sensitive to SOX chemotherapy. As for patients achieve SD or PD, they will be considered as subjects with tumors that are not sensitive to SOX chemotherapy and will be excluded. The purpose of this setting is to answer the question of whether more cycles of preoperative chemotherapy should be applied when it is effective in short-term application. When preoperative chemotherapy shows little effectiveness, other treatments will be recommended instead of continuing to apply chemotherapy. In addition, pre-enrollment can ensure the completion of chemotherapy after randomization and reduce the early termination of chemotherapy due to poor efficacy. Therefore, in our opinion, the design is appropriate.

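### The per-protocol set imposes a post-randomisation chemotherapy condition on Arm A only, probably favouring six cycles on pCR, and the article does not say which analysis set decides the primary comparison

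*Protocol article*

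**What the plan says.** Under Grouping, all patients first receive three cycles of SOX, and only responders go forward: "After tumor response evaluation using RECIST 1.1, patients achieving CR or PR will be enrolled". Randomisation follows. From then on the arms differ. For the longer arm, "patients in Arm A will receive three more cycles of SOX (six cycles of neoadjuvant chemotherapy with SOX in total) followed by D2 gastrectomy". For the shorter arm, "After randomization, patients in Arm B will receive D2 gastrectomy (three cycles of neoadjuvant chemotherapy with SOX in total").

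The Statistical analysis section names two analysis sets. The first is "Both intention-to-treatment analysis (ITT, patients who receive any treatment after enrollment"). The second is "per-protocol analysis (PP, patients who receive all preoperative chemotherapy and surgery) will be performed". It does not say which of the two decides the primary comparison. Sample size calculation confirms what that comparison is: "The primary endpoint of this trial is pCR rate". The same section sizes the trial at 262 per arm with a 10% drop-out allowance, and it does not name the set that the test is run on.

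**The concern.** A per-protocol rule normally conditions on adherence. Here the chemotherapy part of the rule can exclude patients in only one arm. At allocation every Arm B patient has had all the preoperative chemotherapy that the arm calls for. An Arm A patient still has three three-week cycles to go, about 9 weeks, and leaves the set by stopping for toxicity, refusal or progression. An Arm A patient who is resected after four or five cycles is also removed, although the primary endpoint has been observed.

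The excluded Arm A patients probably have fewer pCRs than those who remain. Progression during cycles 4 to 6, or never reaching surgery, rules out a pCR. Taking such patients out of the denominator of one arm can produce an apparent gain for six cycles when the extra cycles do nothing. Early stopping is also part of what a six-cycle policy delivers, so removing it answers a narrower question than the one the trial poses. If the two analyses disagreed, the article gives no rule for which one the pCR conclusion follows.

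**Working it through.** **The plan's own figure.** Inputs from Sample size calculation: pCR 7% and 15%, two-sided α 0.05, power 0.80, 10% drop-out. With unpooled variance for two proportions, n = (0.15×0.85 + 0.07×0.93) × (1.960 + 0.842)² / 0.08² = 0.1926 × 7.849 / 0.0064 = 236.2. Dividing by 0.9 gives 262.4, which agrees with the stated 262 per arm. (The printed formula contains only one variance term and gives about 156 before drop-out. That is a separate matter.)

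**The entry conditions side by side.**

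| Condition for the per-protocol set | Arm A | Arm B |
|---|---|---|
| Cycles 1–3 | met before randomisation | met before randomisation |
| Cycles 4–6 | after randomisation | not applicable |
| Surgery | after randomisation, after cycles 4–6 | after randomisation |

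Only the middle row differs between the arms.

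**Size of the distortion under no true effect.** The article gives neither the proportion of Arm A that will stop early nor the pCR rate of those patients, so both are assumptions and are varied.

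- 262 per arm; pCR 7% of all randomised in both arms (the article's three-cycle figure).
- u = 3% unresected in each arm (assumed).
- f = fraction of Arm A outside the set, 10–25% (assumed). It includes the 3% unresected.
- r = pCR of resected Arm A stoppers relative to the average among resected patients (assumed).

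Per-protocol rates:

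- Arm B: 0.07 / 0.97 = 7.22%, n = 254.1.
- Arm A, no excluded patient with a pCR: 0.07 / (1 − f), n = 262(1 − f).
- Arm A, resected stoppers at relative rate r: [0.07 − (f − 0.03) × r × 0.0722] / (1 − f).

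Rejection probability is the normal approximation to the two-sided pooled two-proportion test, which is equivalent to the planned chi-square test.

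Worked case, f = 20% and no excluded patient with a pCR. Arm A is 0.07/0.80 = 8.75% on 209.6 patients, against 7.22% on 254.1, a difference of 1.53 points. The null standard error is 0.0252 and the actual one 0.0254. The upper tail is 1 − Φ((1.96×0.0252 − 0.0153)/0.0254) = 9.0% and the lower tail is 0.5%, about 9.5% in all.

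| f | Arm A pCR, none in excluded | Rejects | Arm A pCR, r = 0.5 | Rejects | Rejects, r = 1 |
|---|---|---|---|---|---|
| 10% | 7.8% | 5.7% | 7.5% | 5.2% | 5.0% |
| 15% | 8.2% | 7.1% | 7.7% | 5.6% | 5.0% |
| 20% | 8.75% | 9.5% | 8.0% | 6.2% | 5.0% |
| 25% | 9.3% | 13.3% | 8.3% | 7.2% | 5.0% |

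Arm B is 7.2% throughout. With r = 1.5 and f = 25%, Arm A becomes (0.07 − 0.22×1.5×0.0722)/0.75 = 6.2%, so the bias then favours three cycles. At a common pCR of 15%, the same exclusions give 6.5–24.5% if no excluded patient has a pCR and 5.4–10.0% at r = 0.5.

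On all randomised patients, with unresected patients counted as non-pCR, the null difference is 0 and the test keeps its 5%.

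**The case against.** The best defence is that this is a conventional per-protocol analysis. The arms are assigned different amounts of chemotherapy, so adherence means different things by design, and selection on adherence is the known reason for running intention-to-treat alongside it. That stands as far as it goes: a supportive per-protocol analysis is ordinary practice, and its presence is not a fault.

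Four stronger readings are tempting, and the article does not support them.

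- **That the two sets have equal standing.** The text says only that both will be performed. It neither ranks them nor calls them equal, and a ranking may sit in a full protocol or analysis plan that is not shown. What remains is that the published per-protocol definition is one-sided however the sets are ranked.
- **That nothing is asked of Arm B.** Surgery is required after randomisation in both arms. Only the chemotherapy condition is one-sided.
- **That the set must favour six cycles.** A responder who stops for toxicity and is then resected need not have a lower pCR rate. The bias is zero if stoppers match the average and reverses if they do better.
- **That the upper rejection rates are what to expect.** They require every excluded patient to lack a pCR, including those resected and graded.

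The Discussion also offers a safeguard: "pre-enrollment can ensure the completion of chemotherapy after randomization and reduce the early termination of chemotherapy due to poor efficacy". Randomising only responders who have had three cycles should indeed reduce stopping for poor efficacy, which is where the bias is strongest. The stated reason does not reach toxicity or refusal during cycles 4 to 6, and it does not exclude later progression. The Background reports low completion in earlier perioperative trials, but with other regimens and counting postoperative cycles, so it supplies no rate for this trial.

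**Conclusion.** The point holds in a limited form. The asymmetry is a fact of the text: the chemotherapy condition acts after randomisation in Arm A only, and it bears on the primary endpoint. That it favours six cycles is probable but not certain. With no true effect and a 7% pCR rate, the spurious gain over 10–25% exclusion is about 0.6 to 2.1 percentage points if no excluded patient has a pCR, about 0.3 to 1.1 points if resected stoppers have half the average rate, and nil if they have the same rate. The corresponding error rates are 5.7–13.3%, 5.2–7.2% and 5.0%. These rest on assumed exclusion fractions, an assumed 3% unresected per arm, and an assumed pCR rate in stoppers.

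The definition would do little harm in an analysis clearly marked as supportive. The weakness is that nothing in the article prevents the selected set from carrying the pCR conclusion. The point is worth correcting before the data are seen.

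**What to change.** In Statistical analysis:

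1. State that the pCR conclusion rests on all randomised patients in their assigned arm, with patients not resected counted as non-pCR. As the section sends missing data to multiple imputation, it should also say that absence of resection is not a missing pCR value.
2. Label the per-protocol analysis supportive and say that it cannot support a claim on its own.
3. Tabulate by arm the number of patients outside the per-protocol set and the reasons, and show pCR separately for Arm A patients resected after fewer than six cycles.

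The per-protocol set need not be redefined. A version based on resection alone would make the rule the same in both arms but would drop chemotherapy adherence and answer a different question.

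The cost is a few sentences and one table, with no change to treatment or sample size. The downside is that the six-cycle result may look less favourable.
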